### Statistical analyses

Primary and secondary outcomes will be conducted on the intention-to-treat (ITT) sample. A linear mixed-model repeated measures ANOVA with time as a within groups factor and treatment condition as a between-groups factor will be used for the main research question. Mixed-model repeated measures ANOVA uses all available data of each subject and does not involve the substitution of missing values [41]. With regard to the process variable, i.e., the quality of the working alliance, we will conduct Pearson correlations of the WAI with residualized change scores on the primary and secondary outcomes.

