### Recruitment

Forty therapists, all members of the Deutsche PsychotherapeutenVereinigung (DPtV), working in secondary care will be recruited. All therapists are informed about the study by the DPtV and all interested members are invited to participate in the study. Participating therapists inform their self-referred patients about the study and ask them if there are willing to take part in the present study. Potential study participants (patients) are informed about the possibility of taking part in the present study in the initial therapy session by their therapist. Interested patients receive an information sheet and a written informed consent form by the therapists and are invited to ask questions. After returning the completed informed consent form individually to the therapists, participants are asked to complete online screening questionnaires at home to assess whether they fulfill the inclusion criterion of BDI-II-Score > 13.

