### Randomization

Participants who return the informed consent and meet all of the inclusion and none of the exclusion criteria will be randomly allocated to the study conditions (50:50). Randomization takes place at an individual level within therapists. Thus, therapists provide both treatments, allowing us to control for therapist effects. The allocation list will be produced using an automated computer-generated random numbers table placed in a secured web-based database and will be concealed to the investigators and the therapists (www.random.org). After randomization, the participant and his or her therapist will be informed about the condition by email.

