## Discussion

Major depression is a prevalent and debilitating disorder. Even though there is ample evidence for the efficiency and effectiveness of (guided) Internet-based interventions as well as for conventional psychotherapeutic treatments for depression, there are various strengths and limitations for both forms of treatments [11].

In this study, we will examine the effectiveness of psychotherapy plus a web-based online depression program (*deprexis*) versus traditional psychotherapy in routine care. We expect that depression levels of participants in the intervention group will be significantly lower after three months and after six months compared to the control group. Additionally, we will gain valuable experiences in combining an online psychological intervention with routine psychotherapeutic care.

A major strength of this study is that to the best of our knowledge, it will be the first study that tests whether an adjunctive web-based treatment tool in psychotherapy for depression can be successfully integrated in routine care and whether the combination will show additional effects compared to a regular psychotherapy for depression.

There are important limitations in the present study that should be mentioned: First, we adopted a crossed therapist design, i.e., a given therapist delivers the control as well as the experimental condition. This design is associated with potential drawbacks [42] but was necessary to choose in order to be able to run the study in routine care. In order to adjust for the potential downsides of this design, in the analyses we will control for therapist allegiance. Second, we will not have standardized assessments of depression diagnosis but rely solely on clinical diagnoses of experienced, licensed psychotherapists plus an online self-report diagnostic assessment. Third, in the present study, we will use *deprexis* as the only adjunctive web-based intervention tool. Therefore, generalizability of the results to other web-based interventions will be restricted.

In addition to the main analysis described in the methods section, our study will be able to address a number of other important research questions, some of which have not been addressed before. For example, we will be able to assess whether an adjunctive web-based treatment affects working alliance scores. Furthermore, we will assess attitudes towards blended psychological interventions from the patients’ as well as the therapists’ perspective.

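### Patients are randomised within therapist so that therapist effects can be controlled, but the stated main model contains no term for therapist

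*Protocol article*

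**What the plan says.** Under Recruitment: "Forty therapists, all members of the Deutsche PsychotherapeutenVereinigung (DPtV), working in secondary care will be recruited". With 800 patients planned, that is about 20 per therapist.

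Under Randomization: "Randomization takes place at an individual level within therapists". The reason follows at once: "Thus, therapists provide both treatments, allowing us to control for therapist effects".

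Under Statistical analyses, the model for the main research question is "A linear mixed-model repeated measures ANOVA with time as a within groups factor and treatment condition as a between-groups factor". No therapist factor, therapist random effect or therapist-by-condition term is named there or anywhere else in the article.

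The Discussion lists as a limitation that "a given therapist delivers the control as well as the experimental condition", and offers one remedy: "in the analyses we will control for therapist allegiance".

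The sample size section mentions no variance between therapists.

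**The concern.** The article names the factors of its main model and leaves out the one around which the randomisation is organised. Two separate things can follow.

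- **Differences in level.** If some therapists' patients do better than others' in both arms, and allocation is balanced within therapist, this variation is absent from the treatment contrast. A model without therapist still counts it as error, so the precision the design could give is lost.
- **Differences in effect.** If the program helps more with some therapists than with others, patients of one therapist share that deviation. A model without a therapist-by-condition term treats it as independent patient noise, so the standard error is too small for a statement about therapists in general.

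Variation in effect is plausible from the article itself. Therapists decide how far to support use of the program (Description of the interventions), and their orientation ranges from mainly cognitive-behavioural to psychodynamic (Therapists). The Blinding section places the trial's focus on generalising to routine practice, which suggests inference beyond the participating therapists.

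The allegiance adjustment does not fill the gap. As a main effect it can explain only the part of the level differences that goes with allegiance, and it says nothing about how the treatment effect varies from one therapist to another.

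**Working it through.** **Inputs from the article.** N = 800, allocated 1:1; 40 therapists; d = 0.2; two-sided alpha .05; power .80.

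**Assumed, because the article gives no values.** Therapist ICC (rho) of .05 to .10. Between-therapist SD of the treatment effect (s) of 0 to 0.3, in outcome SDs. Exactly 10 patients per arm for each therapist. Total variance 1 within an arm. A comparison at a single time point.

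**1. The plan's own figure.** n per arm = 2 × (1.960 + 0.842)² / 0.2² = 393, so 786 in total (788 with the t distribution). At 400 per arm, power is .807. The planned 800 therefore agrees with a comparison of independent patients with no therapist variance. A change score with a pre-post correlation of .5 gives the same 786; the article does not state its correlation.

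**2. Variances.**
- Reported when therapist is ignored: 2/400 = .00500.
- True: 2 × (1 − rho − s²/4)/400 + s²/40.
- Actual alpha: 2 × [1 − Φ(1.96 × √(reported/true))].

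**3. Therapists differ in level only (s = 0).**

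| rho | true variance | true/reported | actual alpha | power, ignored | power, modelled |
|---|---|---|---|---|---|
| .05 | .00475 | 0.95 | .044 | .814 | .827 |
| .10 | .00450 | 0.90 | .039 | .820 | .846 |

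**4. The effect also varies (rho = .05).**

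| s | true variance | true/reported | actual alpha | power of a correct analysis |
|---|---|---|---|---|
| 0.1 | .00499 | 1.00 | .050 | .81 |
| 0.2 | .00570 | 1.14 | .066 | .75 |
| 0.3 | .00689 | 1.38 | .095 | .67 |

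Simulation at rho = .05 gave .043, .049, .065 and .096 for s = 0, 0.1, 0.2 and 0.3. An analysis of the 40 within-therapist differences held .049 to .053 in the same runs.

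**5. Where the two errors cancel.** Setting true equal to reported gives s² = (2 × rho/400) / (1/40 − 0.5/400). This is s = 0.10 at rho = .05 and s = 0.15 at rho = .10.

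**6. A random intercept alone is not enough.** It reports 2 × (1 − rho)/400. At rho = .05 and s = 0.2 that is .00475 against a true .00570, and alpha is about .074.

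**7. Baseline as a level of time.** If the effect is tested as time by condition, the contrast is a difference in change from baseline. A therapist effect that is the same at baseline and follow-up subtracts out of every patient's change, so step 3 does not apply to it. Simulated change scores gave alpha of about .050 to .054. Only therapist differences in change then matter.

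**8. The balance assumption.** If allocation within therapist is not balanced but simple, the true variance becomes 4 × (1 − s²/4)/800 + s²/40 and rho drops out. Level differences then cost precision but leave alpha near .05. The offset in step 5 also disappears, and alpha is about .06, .07 and .10 at s = 0.1, 0.2 and 0.3. Simulation agrees.

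**The case against.** The strongest reply is that this is one sentence in a condensed article. It names a mixed model but gives no random-effects structure at all, so therapist is unspecified rather than excluded. The Randomization section states the intention to control therapist effects, the allegiance remark shows that the model sentence is not exhaustive, and an unseen analysis plan may contain the term. This has force against any claim that the final analysis will be wrong. It does not remove the mismatch: the article lists its factors, omits the one its design rationale depends on, and puts a different therapist adjustment in its place.

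Three further points stand and limit the finding.

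- A therapist intercept that is constant over time cancels from a time-by-condition test with baseline as a level. On that reading the lost precision disappears, and a plain random intercept would do almost nothing.
- If the program has no effect with any therapist, s is zero and there is no inflation. Inflation needs effects that vary around a zero average and inference beyond these therapists. With d = 0.2 and normally distributed effects, s = 0.2 would mean a reversed effect for about 16% of therapists and s = 0.3 for about 25%, so the upper values are strong assumptions.
- The Randomization section describes an allocation list without blocks or separate lists per therapist. Treating therapist as a formal stratum is a fair reading of its wording, but still a reading.

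**Conclusion.** The point holds as a mismatch between the design and the stated model: patients are randomised within therapist in order to control therapist effects, and the model as written does not use that grouping. It should be fixed.

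A reader might infer that the primary test has an inflated type I error, or that its standard error is certainly wrong. The article does not support that. It gives neither the therapist ICC nor the between-therapist SD of the effect. Over the balanced cases tabulated above, actual alpha runs from .039 to .095, below .05 if only levels differ and above it once s exceeds roughly 0.10 to 0.15. The two errors nearly cancel in that range. Inflation also depends on wishing to generalise beyond the therapists in the trial. Where only levels differ, modelling therapist gains 1.3 to 2.6 percentage points of power, and nothing if the level is constant over time and cancels.

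What can be said firmly is that, as written, the validity of the primary test depends on two unknown variances that the design allows to be modelled.

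**What to change.** State in the primary and secondary models how therapist enters, so that it acts on the post-baseline outcome:

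- with baseline BDI-II as a covariate, a therapist random intercept (for a secondary outcome, its own baseline value as the covariate); or
- with baseline as a level of time, therapist and therapist-by-time random effects.

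Add a random therapist-by-condition term (by time, where baseline is a level), at least as a sensitivity analysis. Use Kenward-Roger or Satterthwaite degrees of freedom and report the estimated between-therapist SD of the effect. Reconcile Randomization, Statistical analyses and the allegiance sentence in the Discussion so that they describe one model.

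The cost is wording. Therapist identity is known for every patient from the randomisation, and the article reports 28 of 800 enrolled, so the change can be made long before results exist. The downside is a wider confidence interval if the effect does vary. At rho = .05, relative to the model without therapist, it is about 7% wider at s = 0.2 (√1.14 = 1.07) and 17% wider at s = 0.3 (√1.38 = 1.17), before the small further widening from using fewer degrees of freedom.

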**Methods/design:**

This study is a currently recruiting pragmatic randomized controlled trial (RCT) that compares regular psychotherapy *plus* a web-based depression program (“deprexis”) with a control condition exclusively receiving regular psychotherapy. Adults with a depressive disorder (N = 800) will be recruited in routine secondary care from therapists over the course of their initial sessions and will then be randomized within therapists to one of the two conditions. The primary outcome is depressive symptoms measured with the Beck Depression Inventory (BDI-II) at three months post randomization. Secondary outcomes include changes on various indicators such as anxiety, somatic symptoms and quality of life. All outcomes are again assessed at the secondary endpoint six months post randomization. In addition, the working alliance and feasibility/acceptability of the treatment condition will be explored.

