## Methods/design

### Design

A two-armed randomized pragmatic RCT is currently being conducted to compare regular face-to-face psychotherapeutic treatment with a combined treatment, i.e., face-to-face psychotherapeutic treatment *plus* a web-based adjunctive treatment tool (*deprexis*). Measurements in both conditions are assessed at baseline (T0), after six weeks (process measures), after three months (T1), and after six months follow-up (after randomization) (T2). The study design is shown in Figure 1.

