### Sample size calculation

Regarding differences between the two active treatment conditions, we want to be able to detect standardized between-groups effects sizes (Cohen’s *d*) of 0.2. Smaller effect sizes are considered to be negligible from a clinical point of view [27]. At an α error level of .05 (two-tailed), a statistical power (1-Beta) of .80, and a correlation between pre- and post-measurements found in our earlier studies, we need to include 800 participants. This sample size calculation is conservative and is based on a current meta-analysis in which a mean effect of *d* = .28 for online depression programs was found [5]. Since in the current study participants in both conditions will receive psychotherapy, a significant reduction of depressive symptoms can also be expected in the control condition. Therefore, a relatively small effect size between conditions, i.e., depression level after three months between *deprexis* plus psychotherapy vs. psychotherapy is expected.

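### The primary model names no baseline adjustment; adjusting for baseline BDI-II would tighten the three-month comparison at no data cost, by an amount that depends on an unstated correlation

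*Protocol article*

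**What the plan says.** The Statistical analyses section gives the main model two factors: "time as a within groups factor and treatment condition as a between-groups factor". It says that all available data of each subject are used without substituting missing values. It does not list the levels of time, say which term or contrast is the primary test, or mention baseline BDI-II as a covariate.

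The Design section and Table 1 place the BDI-II at T0, three months (T1) and six months (T2). The Abstract fixes the endpoint: "The primary outcome is depressive symptoms measured with the Beck Depression Inventory (BDI-II) at three months post randomization". The Sample size calculation section states "At an α error level of .05 (two-tailed), a statistical power (1-Beta) of .80", takes a between-group effect of d = 0.2 as the target, and relies on "a correlation between pre- and post-measurements found in our earlier studies". It reports no value for that correlation and concludes that 800 participants are needed. No SD for the BDI-II appears at any time point. Inclusion requires a baseline BDI-II above 13.

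**The concern.** Baseline BDI-II is measured before randomisation, so the arms have the same expected baseline. A repeated-measures model that treats T0 as one more outcome occasion, with a separate mean in each arm, does not use that fact. Its T1 time-by-condition contrast subtracts the whole observed baseline difference, where regression would subtract only the share that predicts the T1 score.

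The cost is precision. The trial aims at d = 0.2, which the article treats as the smallest effect of clinical interest, and plans for 80% power. Precision that can be had from data already collected is worth taking in that setting.

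**Working it through.** **Inputs.** From the Sample size calculation section: d = 0.2, two-sided α = .05, power .80, N = 800. From the Randomization section: 1:1 allocation, so 400 per arm. Assumed, because the article gives no values: pre-post correlation r from .3 to .7, and k = SD(T0)/SD(T1) of 1 or 0.8. The T1 SD is set to 1.

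**The plan's own figure.** Per arm n = 2v(1.960 + 0.842)²/d², where v is the variance factor of the analysed quantity.
- T1 score alone, v = 1: 393 per arm, 786 in total. This is within 3% of 800; power at 400 per arm is .807.
- Change score, equal SDs, v = 2(1−r): also 786 at r = .5; 800 is hit exactly at r ≈ .49.
- Baseline-adjusted, v = 1−r²: 716, 590 and 402 at r = .3, .5 and .7.

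So 800 fits a calculation with no net gain from baseline. This is not proof of one: at r = .3 an adjusted calculation plus an unstated allowance of 1 − 716/800 ≈ 10% for missing data would also reach 800.

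**Variance factors for the T1 effect.**
- Change contrast: 1 + k² − 2rk, which is 2(1−r) when k = 1.
- Unadjusted T1 level: 1.
- Baseline-adjusted: 1 − r².

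Change minus adjusted is (1 + k² − 2rk) − (1 − r²) = (k − r)², which is never negative. The change contrast can therefore equal the adjusted one (when r = k) but not beat it. With k = 1 the ratio of adjusted to change variance is (1−r²)/[2(1−r)] = (1+r)/2.

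**Variance lost relative to adjustment.**

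| Contrast tested | r = .3 | r = .5 | r = .7 |
|---|---|---|---|
| Change, k = 1 | 35% | 25% | 15% |
| Change, k = 0.8 | 22% | 11% | 2% |
| Unadjusted T1 level | 9% | 25% | 49% |

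Example for k = 0.8, r = .5: change 1 + .64 − .80 = .84; adjusted .75; loss 1 − .75/.84 = 11%.

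On the SE scale the effect is smaller: at r = .5 and k = 1, 1 − √.75 = 13%.

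**Power at 400 per arm, all analysed, k = 1**, from Φ(0.2/√(2v/400) − 1.96):

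| r | Change | T1 level | Adjusted |
|---|---|---|---|
| .3 | 67% | 81% | 84% |
| .5 | 81% | 81% | 90% |
| .7 | 95% | 81% | 98% |

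**Check in the three-occasion model.** Generalised least squares with compound symmetry and 400 per arm at r = .5 gives a variance of .00500 for the T1 − T0 contrast with free T0 means, and .00375 for the T1 effect with T0 means constrained equal. The ratio is .75, as the formula says.

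**The case against.** The strongest objection is that the article does not say T0 is a level of time with free means. The two-factor description would also fit a model with a common T0 mean, which is one of the remedies. Nor is the Statistical analyses section a full list of terms: the Discussion promises control for therapist allegiance and the Randomization section speaks of controlling for therapist effects, and neither appears there. A fuller plan may add baseline. This stands as a limit on certainty. The point concerns the model as described, and a gain remains on either unadjusted reading of the T1 comparison.

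A second objection is that the Abstract and the sample-size text describe a level difference at three months, not a difference in change. This also stands. On that reading the change-score algebra does not apply, but leaving out baseline still costs r².

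A reader might go further and infer three things that the documents do not support.
- That the plan throws away a quarter of its precision. That figure needs r near .5 and equal SDs, neither of which is reported, and it is on the variance scale.
- That a change score is worse than ignoring baseline whenever r is below .5. That threshold also needs equal SDs; at k = 0.8 it is r below .4. The entry cut at BDI-II above 13 may lower r, but it may equally narrow the baseline SD, which shrinks the loss.
- That the analysis is biased or the trial underpowered. The change contrast is unbiased under randomisation, and at r = .5 with equal SDs 800 participants give about 81%, which meets the plan's target if all are analysed.

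**Conclusion.** The point holds as one of efficiency. The stated model names no baseline adjustment, and without it the T1 comparison is never more precise than the adjusted one. The variance loss is about 15% to 35% for a change contrast with equal SDs, about 2% to 22% if the baseline SD is 0.8 of the T1 SD, and 9% to 49% for an unadjusted T1 level difference, all over r = .3 to .7. At r = .5, equal SDs and all 800 analysed, power rises from about 81% to 90%.

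These sizes rest on assumed values of r and of the SD ratio, and on complete data; the article gives no dropout rate. That T0 is a level of time with free means is the natural reading, not a stated fact. The point deserves action because the target effect is small and the remedy is free, not because the planned estimate would be wrong.

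**What to change.** State the primary contrast as the between-arm BDI-II difference at T1, and obtain it in one of two ways:
- a mixed model of T1 and T2 BDI-II with condition, time, their interaction, baseline BDI-II and baseline-by-time; or
- a model of T0, T1 and T2 with the T0 means constrained equal across arms, which also retains patients who have only T0.

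Use the same form for the secondary outcomes measured at baseline (GAD-7, PHQ-15, SF-12, FEP-2 and the empowerment scale). Report the pre-post correlation used in the sample-size calculation, and the form of analysis it was applied to, so that 800 can be matched to the model.

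The cost is a few sentences of analysis text. Baseline BDI-II is already collected from every participant to check eligibility, so no extra data or patient burden is involved. The Trial status section reports 28 of 800 enrolled, so the change can be made early in recruitment.

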Recently, Mansson et al. [20] conducted a proof-of-concept study on the effectiveness of a blended form of psychotherapy in a mixed anxious-depressed sample. The adjunctive web-based platform was to be used at home and in the clinical setting where treatment was provided. The main part of the platform consisted mainly of material that would have been presented on paper or verbally in a face-to-face session. Additionally, the platform comprised some basic components of CBT, such as scheduling sessions, keeping an agenda, and setting goals. Results indicated that this blended treatment had a positive effect across anxious and depressive symptom measures as well as on a quality of life measure in a mixed sample of 15 patients suffering from MDD and/or anxiety disorders. Additionally, patients as well as therapists rated the treatment mostly favorably. Positive patients’ feedback included, for example: memory support and learning, potential to gain an overview of the treatment process, positive implications for homework assignments, promotion of a sense of autonomy and responsibility.

The literature cited above indicates that combining traditional face-to-face psychotherapy and web-based tools may be a promising venue. A possible explanation for these results is highlighted by a recent review, which concludes that patients’ treatment adherence may be improved through new technologies [21]. Potential benefits of blending treatments could for example be a greater reduction of depressive symptoms or more cost-efficacious treatments [19]. However, there could also be some serious downsides of combining conventional face-to-face treatments and new technologies. For example, a recent randomized controlled study showed that appointment reminder via SMS did not lead to higher appointment attendance as expected and, more importantly, that more client dropped out in the reminder condition compared to the no reminder condition [22]. Finally, to our knowledge there is no study that investigates how the blending of treatments affects important process variables such as the therapeutic alliance.

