### Objective and research questions

The main objective of the present study is to further investigate combined treatment approaches for MDD by evaluating an empirically validated web-based treatment (*deprexis;* [23-25]) as an adjunctive tool in regular psychotherapeutic treatment in comparison with traditional psychotherapy in a sample of depressed outpatients by means of a pragmatic RCT in routine care. Therefore, our main hypothesis is that the combined treatment (TAU plus Deprexis) is more effective than regular psychotherapeutic treatment (TAU) alone.

Additionally, during a 6-month period we intend to test on an exploratory basis how helpful patients as well as therapists rate the combined treatment and whether the combination is associated with increased efficiency (i.e., reduction of number of sessions) or with negative side effects (e.g., lower quality of the therapeutic alliance, increased drop-out rate).

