### Outcome measures

#### Depressive symptomatology

The German version of the BDI-II [28] will be the primary outcome measure. The BDI-II is a widely used self-report measure for the assessment of depression severity with good psychometric properties and a completion time of 5-10 minutes. Analogous to a previous study [25] on the efficacy of online depression treatment, we only include patients with a score greater than 13. Scores from 0-13 indicate no or minimal depressive symptoms, scores from 14-19 indicate mild depression, from 20-28 moderate depression, and from 29-63 severe depression.

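### With no BDI-II between baseline and month 3, patients who answer neither later visit give the primary model only a baseline, so the month-3 contrast can be biased in either direction if loss differs by arm

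*Protocol article*

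**What the plan says.** The Design section gives the schedule as baseline (T0), then "after six weeks (process measures), after three months (T1", then six months (T2). Table 1 and the Process measure section show that week 6 holds only the Working Alliance Inventory, rated by patient and therapist. The BDI-II is taken at T0, T1 and T2. Its stated burden is a "completion time of 5-10 minutes" (Depressive symptomatology). Under Primary and secondary outcomes, every assessment is online and a patient who has not answered gets two automatic reminders.

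The Statistical analyses section specifies an intention-to-treat mixed model with time and condition, and on missing values says "Mixed-model repeated measures ANOVA uses all available data of each subject and does not involve the substitution of missing values".

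Drop-out appears in two places. Objective and research questions lists an "increased drop-out rate" among possible side effects of the combination, to be explored. The Background cites a trial of text-message appointment reminders in which "more client dropped out in the reminder condition compared to the no reminder condition". No drop-out rate is stated.

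**The concern.** A likelihood-based mixed model corrects for drop-out only as far as the recorded scores explain it. Between randomisation and the primary endpoint this schedule records no depression score. For someone lost for good before T1, the model therefore predicts the month-3 value from baseline and arm alone, as if that person did as well as completers of the same arm with the same baseline. If patients who are not improving by week 6 tend to stop answering, that prediction is too favourable. The errors cancel in the contrast when the two arms lose similar patients at similar rates. They do not cancel when the rate or the reason differs by arm.

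The trial is unblinded, the outcome is self-reported, and the design treats effects below 0.2 SD as negligible, so a bias of even a few hundredths of an SD matters. An analysis plan cannot repair this later, because it cannot supply a score that was never collected. The mood questionnaires inside the program do not fill the gap either, since controls have no access to it during the study.

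**Working it through.** **The plan's own figure.** The inputs are a target d "of 0.2. Smaller effect sizes are considered to be negligible from a clinical point of view", and "At an α error level of .05 (two-tailed), a statistical power (1-Beta) of .80". Per arm, n = 2(1.960 + 0.842)²/0.2² = 392.5, so 393, or 786 in total. The stated 800 reproduces to within 3%, and power at 400 per arm is 0.807. This match uses no drop-out and no pre-post correlation. It serves here only to set the scale of 0.20 SD.

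**Assumed inputs (the document gives none).**
- Correlations: T0-week 6 0.6, T0-T1 0.5, week 6-T1 0.7.
- True benefit: 0.15 SD at week 6 and 0.20 SD at T1.
- Loss before T1: 20-25% in control and 20-35% in the deprexis arm, with no return at T2.
- Loss mechanism: logit P(lost) = a + b × (week-6 score), with slope b per SD set separately by arm. A higher score is worse.

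**Formula.** Let p be the share lost in an arm. Let Δ be how much worse leavers are at month 3 than completers with the same baseline. The planned model misses pΔ in that arm. With the effect written as control minus deprexis,

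bias = p(deprexis) × Δ(deprexis) − p(control) × Δ(control).

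**Large-sample simulation, true effect 0.200.** The last column assumes that every leaver answered at week 6.

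| Loss, control/deprexis | Slope, control/deprexis | Planned schedule | With week-6 BDI-II |
|---|---|---|---|
| 20%/20% | 0/0 | 0.20 | 0.20 |
| 20%/20% | 0.5/0.5 | 0.202 | 0.202 |
| 20%/30% | 0.5/0.5 | 0.220 | 0.201 |
| 20%/20% | 0/0.5 | 0.238 | 0.199 |
| 20%/30% | 0/1.0 | 0.306 | 0.200 |
| 25%/35% | 0/1.0 | 0.322 | 0.199 |
| 20%/20% | 0.5/0 | 0.162 | 0.20 |
| 25%/25% | 1.0/0 | 0.111 | 0.20 |
| 20%/30% | 0/−0.5 | 0.139 | 0.20 |

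**Check against the formula.**
- Row 4 implies Δ = 0.038/0.20 = 0.19 at slope 0.5. Row 3 should then show a bias of (0.30 − 0.20) × 0.19 = 0.019; the simulation gives 0.020.
- Row 5 implies Δ = 0.106/0.30 = 0.353 at slope 1.0. Row 6 should show 0.35 × 0.353 = 0.124 (simulated 0.122), and row 8 −0.25 × 0.353 = −0.088 (simulated −0.089).

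**Other form of the mechanism.** If loss depends on change from baseline to week 6, the bias is 0.005-0.014 with the same link in both arms. It is about 0.05 with a shared link and 20% against 35% loss. It is 0.08-0.15 with the link in the deprexis arm only, and about 0.09 the other way with the link in control only.

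**Limits of the added score.**
- If only 60% of leavers answered at week 6, the estimates are 0.204-0.237.
- If loss follows the month-3 state instead (20%/30%, slopes 0/1.0), the estimate moves only from 0.396 to 0.335.

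**Precision under random loss.** T0 alone explains 0.5² = 0.25 of the T1 variance. T0 with week 6 explains (0.25 + 0.49 − 2 × 0.6 × 0.5 × 0.7)/(1 − 0.36) = 0.50. At 20% loss, the arm-mean variance is proportional to 0.75/0.8 = 0.9375 as planned, and to 0.50/0.8 + 0.25 = 0.875 with week 6. That is 7% lower if every leaver answered at week 6, and less otherwise.

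**The case against.** The quoted sentence is a correct description of a mixed model, and baseline, three and six months is a coherent schedule for a pragmatic trial. That stands: nothing is misstated, and the point concerns what the fixed schedule leaves out.

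A reader might infer that the protocol expects more drop-out with deprexis. It does not. It lists higher drop-out as something to explore, beside possible gains in efficiency, and the Background also cites a review suggesting that technology may improve adherence. The cited drop-out result concerns appointment reminders.

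A reader might also infer that the bias favours the main hypothesis. The last three table rows show the opposite sign under equally arbitrary assumptions, and the documents give no ground for choosing between them.

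Leaving therapy or the program is not the same as leaving T1 unanswered. Assessments are online with two reminders, and the analysis is by intention to treat. Patients who miss T1 but answer T2 also contribute: if all of them returned, an estimate of 0.308 would fall to 0.257 under assumed T2 correlations. Both facts lower the likely size of the bias but do not remove the gap for those who answer neither visit.

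Finally, the added score looks complete in the table because loss was generated from that same score. The limits under the table are therefore part of the result. Multiple imputation, auxiliary variables and sensitivity analyses are commonly left to the analysis plan, and their absence here is no finding.

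**Conclusion.** The concern holds as a conditional one. The schedule leaves the primary model with only a baseline for patients who answer neither T1 nor T2, although an online contact exists at week 6 in both arms. The month-3 contrast is then unprotected against loss that follows early response and differs by arm. The size runs from nil (equal link and rates), through about 0.02 SD (shared link, 10 points more loss in one arm), to about 0.04-0.12 SD (link in one arm only). The last range is 0.04/0.20 = 20% to 0.12/0.20 = 60% of the target, and the sign is unknown. These figures rest on assumed correlations, 20-35% loss, assumed link strengths and no return at T2. The document supports the possibility of such loss, not its occurrence or direction. This is a cheap improvement to the design rather than an error in the analysis.

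**What to change.** Add the BDI-II to the week-6 online assessment in both arms, and enter it as a time point in the mixed model. Keep month 3 as the primary contrast. For patients already past week 6, treat the value as missing; the Trial status section reports 28 of 800 recruited (28/800 = 3.5%), so nearly all patients could still provide it.

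The cost is 5-10 minutes per patient at a contact already scheduled, a small amendment, and slightly more response burden at week 6. The sample size does not change. The gain is less bias, with full removal only when loss follows the week-6 state and leavers answered at week 6, and a small gain in precision under random loss. Patients lost before week 6 would still have a baseline only.
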